### Statistical analysis

For the graphic description of the flow of the participants throughout the protocol, the CONSORT diagram is used. The intention-to-treat (ITT) method will also be used. In the treatment of the missing values, it will be checked if the loss of data occurs completely at random using Little’s MCAR test, and then, the estimation of the missing values will follow the maximum likelihood method through the EM algorithm [73].

As a step prior to determining the effectiveness of the intervention programs, the homogeneity of the groups will be analysed, taking into account all the variables evaluated and using *χ*^2^ tests and ANOVAs according to the type of variables.

To determine if the treatment is better than the control group, one-factor (type of intervention) ANOVAs and ANCOVAs will be performed for each of the scores in the posttreatment (or second pre measure for the control group on the waiting list) of the continuous treatment outcome variables, using in the ANCOVAs the value of the pretreatment evaluation as covariance. In the case of ANOVAs, the DSM or Games-Howel tests will be used for post hoc analyses depending on whether the assumption of equality of variances is met. In the case of significant differences in the ANCOVAs, the groups will be analysed in pairs using new ANCOVAs. For those variables that do not adjust to normality, the corresponding nonparametric tests will be applied (i.e. Kruskal–Wallis and Mann–Whitney *U* for pairwise comparisons). For the qualitative variables, *χ*^2^tests will be used.

To determine the changes over time, the two basic moments will be analysed first (i.e. the changes from pretreatment to posttreatment or the second premeasure for the control group). Repeated-measures ANOVAs will be performed in a mixed design with an intergroup factor with three levels (the two treatments plus the control group) and an intrasubject factor (pre and post measures). In those variables that do not adjust to normality, the corresponding nonparametric tests will be applied (i.e. Friedman). Additionally, in this case, for the qualitative variables, *χ*^2^ tests will be used.

In a second moment of the analysis of the changes over time, the changes between the pre, post and follow-ups will be analysed only for the two experimental groups. For this, an ANOVA will be applied for each of the outcome variables, including an intergroup factor (with two levels: CBT and CBT-M +) and an intrasubject or repeated measures factor, with five levels (i.e. pre, post, 3 months, 6 months and 12 months). In the application of these ANOVAs, the assumption of sphericity will be verified using the Mauchly test, and where appropriate, the Huynh-Feldt correction will be used. Likewise, ANCOVAs of one factor (type of treatment) will be performed for each outcome variable, using the value of the pretreatment evaluation as covariance.

To determine the differences between the two treatments, the intergroup differences and the interactions between time and type of treatment obtained in the different ANOVAs and ANCOVAs mentioned in the previous point will be addressed.

In all analyses, the Holm–Bonferroni correction will be used to adjust the level of significance for multiple comparisons.

To establish the clinical significance of the changes obtained, *χ*^2^ tests will be used considering the data relative to those variables that present a cut-off point capable of discriminating the clinical improvement of the participants. Likewise, the relative risk of presenting problems of one experimental group with respect to the other at different times of measurement will be calculated. In addition, the McNemar related proportions will be calculated to verify if the percentage of problems is the same or different in the pretreatment and in the different subsequent measurement moments, and the Jacobson-Truax method will be applied by calculating the index of reliable change. This analysis will be supplemented by the calculation of the effect size of each variable.

In the specific analysis of the reabuse or revictimization variables, it is expected that the scores show high asymmetry and kurtosis, so they will be recoded as dichotomous variables (presence vs. absence for each type of violence or abuse) in accordance with the procedure described by Johnson et al. [12].

To establish the effectiveness of the intervention program, adherence to treatment will be evaluated considering the percentage of dropouts in each group, the session in which dropouts occur, the number of sessions attended by the women who complete the treatment and the fulfilment of homework. For this, the two treatment groups will be compared in these variables through *χ*^2^ tests or, where appropriate, one-way ANOVA.

Finally, for the analysis of the variables related to therapeutic success, multiple regression (for the prediction of the values of quantitative variables) or logistic regression (for the prediction of therapeutic success vs. failure) will be applied. In addition, to the extent that each variable allows, moderation and mediation analyses will be performed with the PROCESS macro for SPSS using the procedure described by Hayes [74].

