### Sample size

To determine the target sample size, we considered the effect sizes found in the literature (specifically, the overall effect size—omnibus—calculated in the meta-analysis by Arroyo et al. [5]), which ranges from 0.71 to 1.33. Considering an alpha of 0.05 and a statistical power level of 0.80, a minimum group size of 31 was established. Taking a conservative estimate of the expected dropout rate of 30%, a sample size of 45 women per group will be the target, indicating a total of 135 participants across the 3 experimental conditions (CBT, CBT-M + and WL control group).

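### Filling missing outcomes once by EM and then running ordinary ANOVA/ANCOVA gives wrong inference: inflated type I error if arm is in the EM model, a shrunken effect if it is not

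*Protocol article*

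**What the plan says.** All references are to the protocol article.

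- **Analysis set** (Statistical analysis): "The intention-to-treat (ITT) method will also be used".
- **Missing data** (Statistical analysis): Little's MCAR test is run first, and then "the estimation of the missing values will follow the maximum likelihood method through the EM algorithm". The object of estimation is the missing values themselves, not the parameters of a model fitted to the observed scores.
- **Posttreatment analysis** (Statistical analysis): one-factor ANOVAs and ANCOVAs on posttreatment scores, with pairwise ANCOVAs if the three-arm ANCOVA is significant, and a pre-post repeated-measures ANOVA.
- **Follow-up analysis** (Statistical analysis), for the two active arms: "an ANOVA will be applied for each of the outcome variables", with five time points.
- **Multiplicity** (Statistical analysis): Holm–Bonferroni throughout.
- **Planned size and loss** (Sample size): "Taking a conservative estimate of the expected dropout rate of 30" per cent, "a sample size of 45 women per group will be the target, indicating a total of 135 participants across the 3 experimental conditions".

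The section mentions no multiple imputation, pooling rule, likelihood model on observed data or variance correction. It does not list the variables in the EM model, so the place of treatment arm is open.

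**The concern.** Complete-data ANOVA and ANCOVA count every filled value as an observed woman. EM fills with conditional means, which lie on the regression line without residual scatter. The residual variance is then too small and the apparent sample size too large. What follows depends on a choice that the text leaves open:

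- **Arm in the EM model:** missing women are placed at their own arm's prediction. The estimate is unbiased, but its standard error is too small.
- **Arm not in the EM model:** missing women are drawn towards the pooled prediction, and the difference between arms shrinks.

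This touches the primary outcome, PTSD severity. The comparison of CBT with CBT-M+ is the most exposed. The two programmes share most of their content, so the true difference may be small. An inflated test could credit the positive-memory module with an absent effect, and a diluted estimate could hide a real one.

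**Working it through.** **1. The plan's own sample size.** Inputs from Sample size: "Considering an alpha of 0.05 and a statistical power level of 0.80, a minimum group size of 31 was established", and a standardised effect "which ranges from 0.71 to 1.33". Taking the lower bound and a two-sided test (sidedness is not stated):

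n = 2(1.96 + 0.842)² / 0.71² = 15.70 / 0.504 = 31.1 per group.

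This agrees with the stated 31; an exact t-test calculation gives 32.1. For dropout, 31 / (1 − 0.30) = 44.3, rounded up to 45, and 3 × 45 = 135. The figure reproduces, and this point does not depend on it being wrong.

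**2. Formulae after a single EM fill.** Let d be the fraction of posttreatment scores missing in each arm, completely at random, n = 45 per arm, and σ² the residual variance given the pretreatment score.

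- *Arm in EM.* The information comes from n(1 − d) women, so the true SE is √[2σ² / (n(1 − d))]. The ANCOVA sees n women and a residual variance of about σ²(1 − d), so it reports √[2σ²(1 − d) / n]. The ratio of reported to true SE is 1 − d, and the type I error is about 2[1 − Φ(1.96(1 − d))].
- *Arm not in EM.* A fraction d contributes no difference between arms, so the expected estimate is about (1 − d) times the true effect.

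**3. Numbers put in**, with simulation beside them (pairwise ANCOVA, correlation 0.5; the 30% simulated error shows repeated runs):

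| Loss d | Type I, arm in EM: formula | Simulated | Estimate of 0.71, arm not in EM: formula | Simulated |
|---|---|---|---|---|
| 10% | 7.8% | 8.2% | 0.64 | 0.64 |
| 20% | 11.7% | 11.3% | 0.57 | 0.57 |
| 30% | 17.0% | 17.3–18.2% | 0.50 | 0.49 |
| 40% | 24.0% | 24.7% | 0.43 | 0.42 |

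Standard errors at 30% loss and correlation 0.5 (σ² = 1 − 0.5² = 0.75):

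- Reported: √(2 × 0.75 × 0.7 / 45) = 0.153; simulated 0.152.
- True: √(2 × 0.75 / 31.5) = 0.218; simulated 0.222.

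**4. Interval coverage at 30% loss, correlation 0.5–0.7.** Nominal 95% intervals cover 82–83% with arm in EM and about 60–71% with arm left out. ANCOVA on the observed scores alone is unbiased, with type I error of 4.8–4.9% and 95% coverage. At correlation 0.5 its power is 89.0%, against 88.9% for the fill without arm, so the fill buys no power.

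**5. Other planned tests at 30% loss, arm in EM.**

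- Three-arm omnibus ANCOVA: 23–24%. Check: P(χ²₂ > 5.99 × 0.7²) = exp(−5.99 × 0.49 / 2) = 23%.
- Pairwise ANOVA on posttreatment scores: 11–16% (correlation 0.7 down to 0.3).
- Pre-post change: about 13%.

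**6. The planned sequence.** A simulation of omnibus ANCOVA followed by Holm-adjusted pairwise ANCOVAs (arm in EM, correlation 0.5) gave:

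- 30% loss: a given pair falsely declared in about 10% of trials, familywise error about 23%.
- 20% loss: about 6% and 12%.

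Holm works on p-values that are already too small and does not restore 5%.

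**7. Unequal loss.** With 10% missing on the wait list and 30% on treatment, type I error is 13% with arm in EM. With arm left out, 0.71 is estimated as 0.55, which is 1 − 0.55/0.71 = about 22% shrinkage.

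**The case against.** Four objections have force.

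- **The single fill is a reading.** The section gives one sentence, and a fuller protocol exists that is not shown. However, the sentence names the missing values as what is estimated, complete-data tests follow directly, and no pooling is described. This is a chosen method, not a detail left for later. What stays open is whether arm is in the model, which is why two results are given.
- **A reader might infer that this trial will run at 17–18% type I error.** The documents do not support that. The figure belongs to one unadjusted pairwise ANCOVA at 30% loss, whereas the plan gates pairwise tests on the omnibus test and applies Holm–Bonferroni. The per-pair rate in that sequence is lower (about 10%), while the familywise rate is higher (about 23%).
- **A reader might also infer that 30% of posttreatment scores will be missing in every arm.** The protocol calls its 30% dropout figure conservative and does not equate it with missing assessments. Under intention to treat, women who leave treatment may still be assessed, and wait-list women have no sessions to leave before their two-month reassessment. Hence the range of losses above. Larger harm at follow-up is plausible if losses accumulate, but the documents give no follow-up loss to size it with.
- **The simulated EM uses the pretreatment score alone in most runs.** If the weekly anxiety and depression scores or the wider battery informed it, both effects could be smaller in the treated arms. That range was not computed.

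The version without arm creates no excess false positives; its harm is bias, poor coverage and no gain in power.

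**Conclusion.** The point holds. Following the section as written gives wrong inference whether or not arm enters the EM model.

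- With arm in the model, the estimate is unbiased, but a single unadjusted pairwise ANCOVA errs at about 8%, 11–12% and 18% for 10%, 20% and 30% loss.
- With arm omitted, type I error stays near 5%, but the effect shrinks by roughly the missing fraction, and coverage is well below nominal.

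The sizes rest on assumptions that the protocol does not fix: one filled data set, two-sided tests, pre-post correlation 0.5–0.7, and equal, completely random loss unless stated otherwise. Lower loss reduces the fault but does not remove it. Little's test is no defence, because these errors arise even when the data are missing completely at random. Recruitment already allows for 30% dropout, so the filled values add false precision rather than needed information.

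**What to change.** Replace the single EM fill with an analysis that carries the missing-data uncertainty and includes arm. Either of these is sufficient:

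- a likelihood-based mixed model for repeated measures on all observed scores, with baseline, arm, time and arm-by-time terms; or
- multiple imputation with arm and baseline in the imputation model, the planned ANCOVA in each imputed data set, and pooling by Rubin's rules.

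Adding random residuals to a single fill is not enough: at 30% loss it still gives type I error of about 13% with two arms and 18% with three.

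The cost is a change of wording, slightly more analysis work, and confidence intervals that are wider because they are correct. Recruitment and assessments are unaffected. Therapy-group effects and a missing-not-at-random sensitivity analysis are separate matters that this defect does not require.

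### In the three-group posttreatment comparison, the fallback for non-normal continuous outcomes ignores the pretreatment score; a rank analysis of covariance would keep it at almost no cost

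*Protocol article*

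**What the plan says.** All of this is in the protocol article, Statistical analysis, unless stated otherwise.

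- **Main rule.** To decide whether treatment beats the waiting list, one-factor ANOVAs and ANCOVAs are run on the posttreatment scores of the continuous outcomes, "using in the ANCOVAs the value of the pretreatment evaluation as covariance".
- **Fallback in the same paragraph.** "For those variables that do not adjust to normality, the corresponding nonparametric tests will be applied (i.e. Kruskal–Wallis and Mann–Whitney" U, the latter for pairs).
- **Fallback for change from pre to post.** "In those variables that do not adjust to normality, the corresponding nonparametric tests will be applied (i.e. Friedman").
- **Later analysis over follow-up.** ANCOVAs with the pretreatment score as covariate are planned for each outcome variable with no normality switch, but only for CBT against CBT-M+.
- **Reabuse variables.** These are expected to be markedly asymmetric and are recoded as present or absent.
- **Sample size section.** The group size is set as follows: "Considering an alpha of 0.05 and a statistical power level of 0.80, a minimum group size of 31 was established". The effect size behind it comes from a meta-analysis and is one "which ranges from 0.71 to 1.33". With 30% dropout the target becomes 45 per group.

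**The concern.** A distribution check decides whether an outcome is adjusted for its own baseline. An outcome that passes gets an ANCOVA that uses the pretreatment score. One that fails gets a test of posttreatment scores alone. The protocol gives no reason for giving up the covariate, and a rank-based method that keeps it exists.

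Two things are at stake. First, precision: the pretreatment score is already collected and usually explains part of the posttreatment variation. Second, chance imbalance at baseline stays in the unadjusted comparison. Within one results table, some outcomes would rest on adjusted comparisons with the waiting list and others only on unadjusted ones.

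**Working it through.** **1. Does anything else restore the adjustment?** Friedman is a within-subject test and gives no comparison between groups. The later ANCOVAs leave out the waiting list. So for a continuous outcome judged non-normal, no named analysis compares treatment with waiting list while using the pretreatment score.

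**2. The plan's own figure.** Read 0.71 as a standardised mean difference, with two-sided 5% and 80% power:

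n = 2 × (1.96 + 0.84)² / 0.71² ≈ 31.1 per group.

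This rounds up to 32; at 31 the power is 0.798, so the stated 31 is reproduced to within rounding. Dropout: 31 / 0.70 = 44.3, hence 45. The formula has no baseline term, so the sample size does not appear to rely on adjustment.

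**3. Normal-theory power at 31 per arm, difference 0.71.** Power = Φ(0.71 × √(31/2) / s − 1.96).

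- Unadjusted t test, s = 1: Φ(2.795 − 1.96) = 0.798.
- Mann–Whitney, effective n = 31 × 0.955: 0.780.
- ANCOVA, s = √(1 − r²): 0.834 at r = 0.3, 0.898 at r = 0.5, 0.975 at r = 0.7.

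The correlation r is an assumption. These figures hold for normal scores, whereas the fallback applies only to non-normal ones, so simulation is needed.

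**4. Simulated power, 31 per arm, shift of 0.71 SD, two-sided 5%, women treated as independent, 2,500 trials per row.** The rank ANCOVA here is an ANCOVA on the ranks of both scores.

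| Scores | r | Ordinary ANCOVA | Mann–Whitney | Rank ANCOVA | Mann–Whitney loss against rank ANCOVA (points) |
|---|---|---|---|---|---|
| Normal | 0.3 | 0.816 | 0.760 | 0.788 | 2.8 |
| Normal | 0.5 | 0.883 | 0.765 | 0.854 | 8.9 |
| Normal | 0.7 | 0.973 | 0.768 | 0.954 | 18.6 |
| Mild skew (gamma, shape 4) | 0.3 | 0.826 | 0.846 | 0.868 | 2.2 |
| Mild skew | 0.5 | 0.881 | 0.822 | 0.913 | 9.1 |
| Mild skew | 0.7 | 0.965 | 0.826 | 0.972 | 14.6 |
| Lognormal | 0.3 | 0.812 | 0.946 | 0.957 | 1.1 |
| Lognormal | 0.5 | 0.884 | 0.948 | 0.977 | 2.9 |
| Lognormal | 0.7 | 0.942 | 0.934 | 0.997 | 6.3 |
| Exponential | 0.3 | 0.797 | 0.946 | 0.956 | 1.0 |
| Exponential | 0.5 | 0.872 | 0.954 | 0.980 | 2.6 |
| Exponential | 0.7 | 0.950 | 0.947 | 0.992 | 4.5 |

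The simulation error of one power near 0.8 is about √(0.8 × 0.2 / 2,500) = 0.008. A separate set of runs with Quade's test (2,000 trials per setting) gave Mann–Whitney about 0.73–0.83 against 0.77–0.98. The losses were about 3 points at r = 0.3, 8–10 at 0.5 and 15–20 at 0.7. Null rejection for Quade's test was 4–5.5%.

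**5. Larger effects.** At a difference of 1.0, Mann–Whitney had 0.96–0.97 against 0.97–1.00 for Quade, a loss of about 0–4 points. At 1.33 both were at least 0.998.

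**6. Chance imbalance.** The standard error of a baseline difference is √(2/31) = 0.254 SD. A difference of at least 0.3 SD (z = 0.3 / 0.254 = 1.18) therefore arises in about 24% of trials for a given pair of arms. At r = 0.5 the unadjusted contrast carries 0.5 × 0.3 = 0.15 SD of it, about a fifth of 0.71.

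**The case against.** The strongest reply is that the fallback costs little and may even help. A reader might infer that switching from the planned ANCOVA to Mann–Whitney loses about 10 points of power for any non-normal outcome. The protocol and the calculations do not support that. Under strong skew, Mann–Whitney beats ordinary ANCOVA at correlations of 0.3 and 0.5 and about equals it at 0.7. With a different skewed model (exponential transform of a shifted normal score), ordinary ANCOVA against Mann–Whitney was 0.730 against 0.765 at 0.3, 0.802 against 0.768 at 0.5 and 0.912 against 0.758 at 0.7. The sign of the difference depends on a correlation that the protocol does not give. This objection stands. The fair comparator is a rank analysis that keeps the baseline, and against that Mann–Whitney lost in every setting run.

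Other points also stand:

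- **Validity.** A reader might infer that the rank tests are invalid because of chance imbalance. Leaving out a baseline covariate does not inflate the type I error of a randomised comparison. Imbalance affects the estimate in the trial at hand.
- **Scope.** Not every outcome has a pretreatment value: the weekly OASIS and ODSIS are described only at the end of each session. The reabuse variables are dichotomised, and the CBT versus CBT-M+ comparison keeps its ANCOVA.
- **Primary outcome.** The EGEP-5 severity score is not exempt from the switch, but nothing in the protocol says that it will be non-normal.
- **Wording.** The named tests are the usual counterparts of one-factor ANOVA, so the ANCOVA might be meant to run beside them. The protocol does not say so, and as written the rank tests are the only analysis named for non-normal variables at this step. The fix settles either reading.

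**Conclusion.** The point holds as a matter of efficiency. For continuous outcomes with a pretreatment value that are judged non-normal, the three-group posttreatment comparison falls back on valid tests that ignore that value. Against a rank analysis of covariance on the same women, the loss is about 3 points of power at a correlation of 0.3, 8–10 at 0.5 and 15–20 at 0.7. Under strong skew it is about 1–6 points, and at a difference of 1.0 about 0–4. These figures assume 31 evaluable women per arm, a difference of 0.71 unless stated, two-sided 5% and independent observations. The correlation is assumed, not documented. Whether any outcome, the primary one included, will trigger the fallback cannot be told from the protocol.

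**What to change.** Replace the fallback sentence with one along these lines: *For continuous outcomes with a pretreatment value whose ANCOVA residuals depart clearly from normality, the groups will be compared with a rank analysis of covariance (Quade), with the pretreatment score as covariate, overall and then in pairs; Kruskal–Wallis and Mann–Whitney U tests will be reported as a sensitivity analysis.*

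Judging normality on the residuals matters because ANCOVA needs roughly normal residuals, not normally distributed raw scores. The planned Holm–Bonferroni correction can stay as it is.

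The change costs one sentence and needs no new data, visits or participants. The small downside is a less familiar test run in two steps: regress the ranks of the posttreatment score on the ranks of the pretreatment score, then compare the residuals between groups.

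### For non-normal outcomes the plan replaces the three-arm pre/post mixed ANOVA with Friedman, which has no arm factor, so the arm-by-time comparison is lost; the rank test that still compares arms ignores baseline

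*Protocol article*

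**What the plan says.** All of this is in the Statistical analysis section of the protocol article, which sets out three linked steps.

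- **Treatment against control.** "To determine if the treatment is better than the control group, one-factor (type of intervention) ANOVAs and ANCOVAs will be performed" on the posttreatment score, with the pretreatment value as covariate in the ANCOVAs. The fallback for non-normal variables is "Kruskal–Wallis and Mann–Whitney *U* for pairwise comparisons".
- **Change over time.** "To determine the changes over time, the two basic moments will be analysed first", meaning pretreatment to posttreatment, or to the second measure for wait-list. The model is: "Repeated-measures ANOVAs will be performed in a mixed design with an intergroup factor with three levels (the two treatments plus the control group"), crossed with a two-level time factor. The fallback is: "In those variables that do not adjust to normality, the corresponding nonparametric tests will be applied (i.e. Friedman").
- **CBT against CBT-M+.** This is to be judged from "the intergroup differences and the interactions between time and type of treatment obtained in the different ANOVAs and ANCOVAs" already described.

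Friedman is the only replacement named for the mixed ANOVA, and it is introduced with i.e. rather than as an example. No nonparametric counterpart of the interaction appears anywhere in the section.

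**The concern.** With three arms and two times, the arm-by-time term of the mixed ANOVA tests whether mean change differs between arms. It is the part of that model that speaks to the randomised comparison of change. Friedman ranks each woman's own values and never uses her arm. For any continuous outcome judged non-normal, which could include the primary EGEP-5 score, the analysis of change would then report only whether women changed. It would not report whether they changed more in one arm than in another.

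The gap matters most for CBT against CBT-M+, the trial's novel question, because the plan says it will draw on the interactions there. Friedman results listed arm by arm also invite a reader to treat a significant result in one arm and a non-significant result in another as a difference between arms.

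There is a smaller, related loss. The fallback that does compare arms uses the posttreatment score alone, so a non-normal outcome also loses the baseline adjustment that the ANCOVA would have given. None of the named fallbacks both compares arms and uses baseline.

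**Working it through.** **1. The plan's own figures.** From the Sample size section: effect size 0.71 (the lower end of 0.71 to 1.33), alpha 0.05 (two-sided assumed), power 0.80. Then n = 2 × (1.960 + 0.842)² / 0.71² = 31.1 per group, against the stated 31 (32 if rounded up; power at 31 is 0.798). Inflating for 30% dropout: 31 / 0.70 = 44.3, so 45, and 3 × 45 = 135. These agree with the plan. They supply the group sizes used below; the structural point does not depend on them.

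**2. What Friedman becomes with two times.** For n women and k times, Q = 12 / [n k (k+1)] × ΣRⱼ² − 3n(k+1), where Rⱼ is the rank sum at time j. Let b women fall and c women rise, with no ties, so b + c = n. The rank sums are n + b at pre and n + c at post. Putting k = 2:

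Q = (2/n) × [(n+b)² + (n+c)²] − 9n = (b − c)² / n.

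This is the sign test. Only the total numbers who fell and rose enter it. Reassigning the women to arms in any way leaves Q unchanged, so Q carries no information on arm or arm-by-time.

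**3. Size by simulation.** Assumptions: pre/post correlation 0.5, independent women, 3,000 to 4,000 runs. Neither the correlation nor the distribution is in the documents.

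| Scenario | Result |
|---|---|
| 45 per arm, all arms improve 0.3 SD | pooled Friedman significant 80%; CBT-M+ significant and wait-list not, 21% |
| 45 per arm, all arms improve 0.5 SD | pooled Friedman significant 99.5%; CBT-M+ significant and wait-list not, 20% |
| 31 per arm, all arms improve 0.4 SD | Friedman run per arm: at least one arm significant and another not, 74% |
| 31 per arm, wait-list worse by 0.71 SD, CBT unchanged, CBT-M+ better by 0.71 SD | pooled Friedman significant about 4%; Kruskal–Wallis on the post score over 99% |

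Pooled Friedman is nearly always significant when the arms do not differ but all improve, and rarely significant when the arms are strongly opposed.

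**4. The fallback that does compare arms.** Kruskal–Wallis on the posttreatment score rejects in about 5% of runs when the arms do not differ, so it is valid. With 31 per arm, log-normal scores, correlation 0.5 and both treatments 0.71 SD (log scale) better than an unchanged wait-list, power is:

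- Kruskal–Wallis on the post score (planned): 79%
- Rank ANCOVA (post on arm and baseline): 89%
- Kruskal–Wallis on change scores: 57%

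With normal data, 31 per arm and both treatments 0.5 SD better, power for Kruskal–Wallis on post, rank ANCOVA and ANCOVA is 47%, 58% and 61% at correlation 0.5, and 47%, 75% and 80% at correlation 0.7. The loss from ignoring baseline grows with the correlation.

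**The case against.** The strongest reply is that the plan does not ask Friedman to compare arms. Treatment against wait-list belongs to a separate paragraph with its own rank fallback, which is valid under randomisation. The Friedman sentence stands under change over time, and a pooled test that detects a real common improvement answers that question correctly. This stands. A reader might infer that a non-normal outcome would have no valid test of treatment against wait-list. The documents do not support that: Kruskal–Wallis with pairwise Mann–Whitney U on the posttreatment score remains, and the pairwise step also covers CBT against CBT-M+ at posttreatment. Nor are the 80% and 99.5% above false-positive rates of anything the plan claims. They would mislead about arms only if Friedman were read as an arm comparison, and the plan nowhere says that it will be.

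Two further readings are tempting but rest on condensed wording. One is that the χ² tests named next ("Additionally, in this case, for the qualitative variables") ignore pairing. The text does not say what is cross-tabulated, the tests could compare arms, and McNemar is planned later in the section for pre against later proportions. The other is that normality will be checked on raw variables rather than residuals. That may be shorthand, and how assumptions are checked is commonly left to a full analysis plan.

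It can also be said that the CBT against CBT-M+ question draws on intergroup differences and ANCOVAs as well as interactions, and that Friedman is named only for the pre/post step, since the five-level follow-up ANOVA has no stated fallback. Both are true and limit the reach of the point. They do not remove it: the mixed ANOVA has an arm factor, its named substitute has none, and the plan later relies on the term that disappears.

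**Conclusion.** The point holds in this scope. For outcomes judged non-normal, the named substitute for the three-arm pre/post mixed ANOVA cannot give the arm-by-time term, so that part of the CBT against CBT-M+ evidence is lost. This follows from the form of the test and needs no assumption about the data.

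Treatment against wait-list is still validly tested on the posttreatment score. The loss there is precision: 79% against 89% power in the log-normal case, and from 47% against 58% to 47% against 75% in the normal cases. These figures rest on the assumed distributions, correlations, effects and 31 per arm, and they treat women as independent.

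The consequence is moderate. It arises only for variables that fail the normality check, and it is repaired by wording.

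**What to change.** For continuous outcomes judged non-normal, replace both Friedman and the unadjusted Kruskal–Wallis with one between-arm method that keeps baseline. Suitable choices are rank ANCOVA, a proportional-odds model with arm and baseline, or the planned ANCOVA with bootstrap or robust standard errors. Name the choice in advance and state that it supplies the CBT against CBT-M+ contrast for these outcomes in place of the missing pre/post interaction.

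Keep Friedman, if wanted, only to describe change within an arm, and say that it will not be used to compare arms. Kruskal–Wallis on change scores is not recommended as the replacement: in the log-normal case above it has less power (57%) than the post-score test already planned (79%).

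The cost is a small amount of extra analysis work. No new data, visits or participants are needed.
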